### Chemotherapy

#### Concurrent chemotherapy

For stage III patients, concurrent cisplatin (100 mg/m², d1-3, Q3w, maximum to three cycles) will be administrated with radiotherapy. For stage II patients, the use of concurrent chemotherapy will be determined by the discretion of physicians. T2N0-1 patients with all nodes < 3 cm, no level IV or Vb nodes involvement, no extranodal extension [ENE] and pretreatment Epstein-Barr virus [EBV] DNA < 500 copies/mL may be considered as candidates of RT alone. Stage I patients will receive radiotherapy alone.

#### Induction and consolidation chemotherapy

The application of induction chemotherapy and consolidation chemotherapy is dependent on the physician’s discretion.

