**Methods:**

ISRT-NPC is a prospective, multicenter, open-label, noninferiority, phase III randomized controlled trial. A total of 414 patients will be randomly assigned in a 1:1 ratio to receive ISI or ERI. Randomization will be stratified by institution scale and N stage. Generally, in the ISI group, the high-risk CTV1 (dose: 60 Gy) includes a 1-cm expansion of the positive LN as well as the VIIa and the retrostyloid space above the bilateral transverse process of the atlantoaxial spine (C1), regardless of N status. The low-risk CTV2 (dose: 50 Gy) covers the cervical nodal region with a 3-cm caudal expansion below the transverse process of C1 for N0 disease and a 3-cm expansion below the positive LN for positive LNs.

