## Methods

### Study design

This study is designed as a multicenter, noninferiority, subject-blinded, randomized, phase III trial. A total of 414 patients harboring stage I-III NPC with LB-LN (detailed definition is presented in “Inclusion criteria” section) from eight tertiary hospitals in China will be randomized (1:1) to the ISI or ERI groups. The flow chart and study design schedule are presented in Fig. 1; Table 1, respectively.

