### Randomization

An eligibility checklist and patient consent must be completed and obtained before randomization. Eligible patients will be allocated randomly to the ISI and ERI groups on a 1:1 basis using a computer-generated randomization scheme with a block size of four. Randomization will be stratified by institution scale (large vs small) and N stage (N0 vs N1 vs N2).

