### Pre-treatment evaluation (baseline)

The enrolled patients are required to complete the following examinations within 4 weeks before registration:

Thorough medical history and physical examination: evaluation of KPS score, weight, height, vital signs, and physical examination of the nasopharynx, cervical LNs, and nervous system.Laboratory tests: blood routine examinations, biochemistry evaluations, urine and stool routine analysis, circular lymphocyte phenotyping, and measurement of Epstein–Barr virus (EBV) DNA concentration.Radiological imaging examinations: fiberoptic nasopharyngoscopy and tumor biopsy, MRI and CT contrast imaging of the nasopharynx and neck, cervical ultrasound, chest CT, abdominal CT/ultrasound, emission computed tomography (ECT) bone scans, and positron emission tomography (PET)/CT (optimal; performed at the discretion of the attending physician).Baseline documentation: electrocardiogram, pulmonary function, and QoL assessment.

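### Discretionary chemotherapy is chosen by a physician who knows the arm, and the article does not place that choice before allocation

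*Protocol article*

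**What the plan says.** All references are to the protocol article.

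- **Induction and consolidation chemotherapy:** "The application of induction chemotherapy and consolidation chemotherapy is dependent on the" physician's judgement. No criteria or decision time are given.
- **Concurrent chemotherapy, stage II:** "the use of concurrent chemotherapy will be determined by the discretion of physicians". A permissive guide, the same for both arms, lists features of T2N0-1 patients who might go without it; it ends "DNA < 500 copies/mL may be considered as candidates of RT alone".
- **Concurrent chemotherapy, other stages:** cisplatin is fixed for stage III. For stage I, "Stage I patients will receive radiotherapy alone".
- **Randomization:** "An eligibility checklist and patient consent must be completed and obtained before randomization". A chemotherapy plan is not among the items named. Strata are institution scale and N stage.
- **Blinding:** the abstract says "ISRT-NPC is a prospective, multicenter, open-label, noninferiority, phase III randomized controlled trial"; Study design says "This study is designed as a multicenter, noninferiority, subject-blinded, randomized, phase III trial".
- **Pre-treatment evaluation (baseline):** "The enrolled patients are required to complete the following examinations within 4 weeks before registration". The list includes staging imaging and EBV DNA.
- **Statistical analysis:** intention-to-treat (ITT) and per-protocol (PP) analyses are planned, and implementation will be compared between the groups from the case report form.

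**The concern.** Under either description of blinding the treating physician knows the arm, because the nodal target volume is contoured by arm (Radiotherapy, Table 2). If chemotherapy is chosen with that knowledge, use may differ between the arms for reasons unrelated to the patient. A physician uneasy about a smaller volume might add chemotherapy in the involved-site (ISI) arm. One concerned about toxicity from the larger volume might withhold it in the elective (ERI) arm, or behaviour might run the other way.

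The Background credits newer induction and consolidation regimens with better outcome in general, and says that combining chemotherapy with radiotherapy worsens toxicity. An imbalance could thus touch both parts of the intended conclusion: preserved regional control, and less toxicity with better quality of life. More chemotherapy in ISI would push RRFS towards non-inferiority; more in ERI would push against it. Since discretionary use is not a deviation, ITT keeps the difference and PP, as described, has no ground to remove it.

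**Working it through.** **1. The plan's own figure.** Inputs from Sample size calculation: 96% at 3 years in both arms, margin 6 points, one-sided 2.5%, power 85%, 5% dropout.

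n per arm = (1.960 + 1.036)² × 2 × 0.96 × 0.04 / 0.06² = 191.5, so 192 per arm and 384 in total. 384 / 0.95 = 404.2, so 405. The stated 414 is within 3% of this. Evaluable per arm: 414 × 0.95 / 2 = 196.65, which gives power 85.9%.

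**2. Illustration.** The documents give no chemotherapy rate, no difference by arm and no effect on regional failure, so these inputs are assumed:

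- f = share of the arm on which the discretionary choice can act. 0.9 or 0.8 excludes 10% or 20% in stage I. 0.5 is a sensitivity value, explained under step 4.
- s = excess use in ISI among those patients.
- r = relative reduction in regional failure from the extra chemotherapy.
- ISI truly at the margin: 3-year failure 10% against 4%.

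ISI failure p = 0.10 × (1 − f·s·r)

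SE = √[p(1−p)/196.65 + 0.04 × 0.96/196.65]

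P(claim non-inferiority) = Φ[(0.06 − (p − 0.04))/SE − 1.96]

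With no imbalance, p = 0.10 and the error is 2.50%.

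| f | s = 0.1, r = 0.2 | s = 0.2, r = 0.3 | s = 0.3, r = 0.5 |
|---|---|---|---|
| 0.9 | p = 0.0982; 2.94% | p = 0.0946; 4.05% | p = 0.0865; 7.96% |
| 0.8 | p = 0.0984; 2.89% | p = 0.0952; 3.84% | p = 0.0880; 7.06% |
| 0.5 | p = 0.0990; 2.74% | p = 0.0970; 3.28% | p = 0.0925; 4.85% |

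Middle case with f = 0.9, worked: f·s·r = 0.9 × 0.2 × 0.3 = 0.054; p = 0.0946; SE = 0.02512; (0.1000 − 0.0946)/0.02512 − 1.96 = −1.745; Φ = 4.05%. In events this is about one regional failure fewer in the ISI arm (196.65 × 0.0054 = 1.06).

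**3. What it takes to reach 5%.** The error is 5% when f·s·r = 0.0785. The excess use needed is s = 0.0785/(f·r):

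| f | r = 0.2 | r = 0.3 | r = 0.5 |
|---|---|---|---|
| 0.9 | 44% | 29% | 17% |
| 0.8 | 49% | 33% | 20% |
| 0.5 | 79% | 52% | 31% |

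**4. Why f = 0.5 is worth showing.** The first two rows of each table spread regional failures evenly over everyone outside stage I. The Background gives 5-year RRFS of 97.6%, 97.5% and 94.6% for N0, N1 and N2, so failure is 2.4%, 2.5% and 5.4%: about twice as high in N2. N2 disease is stage III, where concurrent cisplatin is fixed and only induction and consolidation can vary. The stage II choice acts on patients who fail less often. A smaller effective share is therefore plausible, though its value is not in the documents.

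**5. Reverse direction.** Take true failure of 4% in both arms and excess chemotherapy in ERI, so that ERI failure is 0.04 × (1 − f·s·r). Power falls from 85.9% to 85.4-81.5% (f = 0.9) or 85.4-82.1% (f = 0.8) over the same range of s and r.

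**The case against.** The strongest reply is that this is an absence in a condensed article. The full protocol may fix the timing, the two items named before randomisation need not be the only ones recorded, and the article does not place randomisation relative to the start of induction. That stands as a limit. A reader might infer that the choice is in fact made after allocation; the documents do not show this. They show only that discretion is granted without a limit in time.

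Discretionary chemotherapy is also a defensible choice for stages I-III, and a reader who takes the discretion itself as the error goes too far. The exposure is bounded by fixed treatment in stage I, fixed concurrent cisplatin in stage III, the common stage II guide, and stratification by N stage, which balances a main driver of the choice. The planned comparison of implementation could reveal an imbalance. Those limits stand, but none stops a choice influenced by the arm, and a table of delivered treatment cannot by itself say why the arms differ.

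Finally, a reader might infer serious error inflation. Shifting the ISI rate directly by 2 points, with 196 per arm, gives an error of about 13% or, in the other direction, power of about 44%. From 10% failure, that shift needs f·s·r = 0.20, for example 74% excess use with r = 0.3 and f = 0.9. The power figure needs chemotherapy imbalance alone to raise ISI failure from 4% to 6%. Nothing in the documents supports imbalances of that size.

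**Conclusion.** The point holds at low severity. Stage II concurrent, induction and consolidation chemotherapy are left to a physician who knows the arm, and the article does not put the choice before allocation. Treatment that differs by arm is therefore permitted, and neither analysis set as described would correct it.

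The direction is unknown and the size cannot be derived from the documents. Under the middle assumptions the one-sided error moves from 2.5% to about 3.3-4.05%, and only if ISI is truly 6 points worse. Small imbalances matter little. It does not follow that the trial is biased or that ISI patients will receive more chemotherapy: the documents give no rate, no difference by arm and no effect on regional failure. The case for acting rests on the low cost of the safeguard, not on a demonstrated effect.

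**What to change.** For patients still to be randomised, add to the randomisation form, completed before the arm is released:

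- planned induction chemotherapy (yes/no);
- for stage II, planned concurrent chemotherapy (yes/no);
- planned consolidation (yes/no, provisional).

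The plan should be followed unless a documented clinical reason, such as toxicity, justifies a change. Report planned versus delivered chemotherapy by arm, with reasons for departures. Any analysis restricted to patients treated as planned should be labelled supportive, because that restriction is made after randomisation. If the full protocol already records the plan before allocation, a sentence saying so is enough.

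This is feasible: staging and EBV DNA are available before registration, and the stage II guide uses baseline features only.

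The cost is three form fields, one reason-for-change field, one table and slightly less clinical flexibility. The fix reduces the risk but does not remove it, since departures are still decided with the arm known and consolidation is only provisional. It cannot reach patients already enrolled since recruitment began in August 2022. For them, report delivered chemotherapy by arm and, where recorded, its start date relative to randomisation.

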#### Follow-up

During the treatment course, all enrolled patients will be examined and treatment-related adverse events will be carefully documented weekly. Patients will be followed up at least every three months in the first two years, six months in the third to fifth year, and then yearly. The detailed schedule and examination items are shown in Table 1.

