**Fig. 1 Fig1:**
[figure not shown]
Flow chart showing the overview of this trial. CTV1, high-risk clinical target volume for the nodal region; CTV2, low-risk clinical target volume for the nodal region; C1, the atlantoaxial spine; ENE, extranodal extension; GTV, Gross tumor volume; Gy, gray; LN, lymph node; MAD, maximum diameter; QoL, quality of life; RPLN, retropharyngeal lymph node

**Table 1 Tab1:** Schedule of study assessment

Period	Pre-RT	During RT			within 2 years after RT	3–5 years after RT	5 years after RT
Time		Weekly	Mid	End	every 3 months	every 6 months	annually
Eligibility	X						
Written informed consent	X						
History	X						
Baseline documentation^$^	X						
Physical examination	X	X	X	X	X	X	X
General laboratory tests^#^	X	X	X	X	X	X	X
EBV-DNA measurement	X	X	X	X	X	X	X
Radiological image examinations							
Nasopharyngoscopy	X		X	X	X	X	X
MRI of nasopharynx and neck	X		X	X	X	X	X
Cervical ultrasound	opt		opt	opt	opt	opt	opt
CT of chest and abdomen	X				every 6 months	X	X
Abdominal CT/ultrasound	X				every 6 months	X	X
ECT bone scan	X				annually	annually	X
PET/CT	opt				opt	opt	opt
Toxicities/Adverse events reporting	If related to study procedures	X	X	X	X	X	X
Quality of life	X		X	X	X	X	X

*RT *Radiation therapy, *EBV *Epstein–Barr virus, *CT *Computed tomography, *ECT *Emission computed tomography, *MRI *Magnetic resonance imaging, *PET *Positron emission tomography.

General laboratory tests include blood routine analysis, biochemistry analysis, urine and stool routine analysis, circular lymphocyte phenotyping, and EBV-DNA measurement. $ includes electrocardiography, pulmonary function measurements, and assessments of hypotension and diabetes.

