### Secondary endpoint

The effects of ISI on 3-year OS (measured from registration to documented death from any cause or last follow-up), distant metastasis-free survival (DMFS, measured from registration to documented distant metastasis or death from any cause), and progression-free survival (PFS, measured from registration to documented locoregional recurrence or distant metastasis or death from any cause); early (from the start of radiotherapy until the 1 month after radiotherapy) and late toxicities; and general and late toxicity-related QoL will be evaluated.

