#### Assessment of toxicity and QoL

Acute treatment-related toxicities will be graded using the National Cancer Institute Common Terminology Criteria for Adverse Events (CTCAE) version 5.0. The Radiation Therapy Oncology Group (RTOG) and European Organization for Research and Treatment of Cancer (EORTC) late radiation morbidity scoring schemes will be used to assess late radiation toxic effects. The EORTC QLQ-C30 and EORTC QLQ-H&N35 questionnaires will be applied to evaluate the general QoL. The Groningen Radiation Therapy Induced Xerostomia questionnaire (GRIX) will be used to assess the QoL associated with serostomia. The MD Anderson Dysphagia Inventory (MDADI) composite score and Swallowing Quality of Life Questionnaire (SWAL-QoL) will be used to evaluate swallowing capacity and dysphagia-related QoL.

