### Statistical analysis

The case distribution between the ISI and ERI groups in each center will be described. Compliance will be assessed according to the case report form to compare implementation between the two groups. Total drop-out rates and adverse event drop-out rates will be compared between the two groups using Fisher’s exact test. Baseline comparisons will be performed by using *t*-tests or non-parametric tests for continuous data. Chi-square test will be used to compare categorical data. Both intention-to-treat (ITT) and per-protocol (PP) analysis will be used to assess the efficacy of ISI. Safety analysis will be performed in the safety population. Time-to-event data will be censored in the absence of observations of regional failure at the date of last follow-up or loss to follow-up. The Kaplan–Meier method will be used to estimate the survival rates. Differences between treatment groups will be assessed using log-rank tests. Interaction analysis for RRFS will be undertaken to assess whether differential effects were present between ISI and ERI in predefined subgroups. Adverse events will be listed and analyzed using the chi-square test or Fisher’s exact test. Serious adverse events should be listed in detail and compared between groups. The principal investigator and the protocol committee will perform the analysis. A Data Monitoring Committee (DMC) will be set up to oversee the trial and to decide whether the trial should be stopped.

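### Follow-up and toxicity text tie adverse-event recording and grading to relatedness, Table 1 and the analysis do not, and no assessor is stated to be blinded

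*Protocol article*

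**What the plan says.** Two places in the protocol article link recording or grading to cause:

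- Follow-up, for the treatment course: "treatment-related adverse events will be carefully documented weekly".
- Assessment of toxicity and QoL, acute: "Acute treatment-related toxicities will be graded using the National Cancer Institute Common Terminology Criteria for Adverse Events (CTCAE) version 5.0". For late effects, the RTOG/EORTC "late radiation morbidity scoring schemes will be used to assess late radiation toxic effects".

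Three places do not:

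- Table 1, row on toxicities and adverse-event reporting: the condition "If related to study procedures" stands in the Pre-RT cell only. Every cell during radiotherapy and follow-up is a plain X.
- Statistical analysis: "Adverse events will be listed and analyzed using the chi-square test or Fisher’s exact test", and "Serious adverse events should be listed in detail and compared between groups". Drop-outs due to adverse events are also compared.
- Secondary endpoint: the endpoint is "early (from the start of radiotherapy until the 1 month after radiotherapy) and late toxicities".

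On blinding, the abstract states: "ISRT-NPC is a prospective, multicenter, open-label, noninferiority, phase III randomized controlled trial". The Study design section instead calls the trial subject-blinded. Neither blinds the clinicians, and no blinded toxicity assessor is described.

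**The concern.** The arms differ in the nodal target volume (Table 2), so whoever contours the plan knows the allocation. The Background states the hypothesis that ISI lowers treatment-related toxicity. If an event must be judged related before it is graded, and the clinician who decides knows the arm and shares that expectation, the same symptom may be called related more often after elective region irradiation (ERI) than after ISI. The recorded rates would then differ even with equal true rates.

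Early and late toxicity are secondary endpoints. Together with quality of life, they carry much of the benefit that would justify a 6-point non-inferiority margin on regional control. A clinician grade that was never assigned is hard to reconstruct later. The two sets of instructions also leave room for sites to record differently.

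**Working it through.** **1. Reading check.** From the start of radiotherapy, Table 1 tells a site to report adverse events at each visit with no condition. The Follow-up text tells the same site to document treatment-related events weekly. The toxicity section gives a grading scale for treatment-related acute effects and for late radiation effects, and no instruction for grading an event judged unrelated. The analysis then tests adverse events without restriction. A site could follow Table 1 and record everything, or follow the text and record and grade only related events. Both readings are open.

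**2. Which events a filter could remove.**
- Acute events: the wording is treatment-related. Chemotherapy is part of treatment in this trial, so an acute event attributed to chemotherapy still qualifies. Only attribution to tumour, comorbidity or another outside cause could drop it.
- Late events: the wording refers to radiation effects, so attribution to chemotherapy could also drop an event. Induction and consolidation chemotherapy, and concurrent chemotherapy in stage II, are at the physician's discretion, which makes this attribution harder.
- Lymphopenia: not at risk. Blood counts and lymphocyte phenotyping are scheduled for everyone in Table 1.
- Dysphagia and xerostomia: partly covered by patient questionnaires, which need no attribution.

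**3. Size, by illustration.** The document gives no toxicity or attribution rates, so there is no figure of the plan's own to reproduce here. The total of 414 is set for the primary endpoint and enters only as arm size: 414 / 2 = 207.

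Let p be the true rate in both arms, and a(ERI) and a(ISI) the assumed proportions judged related. The recorded rates are p × a, and

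SE = sqrt[r1(1 − r1)/n + r2(1 − r2)/n], z = (r1 − r2)/SE,

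with the chance of a two-sided 5% result = P(Z > 1.96 − z) + P(Z < −1.96 − z).

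*Assumed p = 40%, n = 207, attribution 95% v 80%:*
- r1 = 0.40 × 0.95 = 0.38; r2 = 0.40 × 0.80 = 0.32; spurious difference 6 points.
- SE = sqrt[(0.2356 + 0.2176)/207] = 0.0468; z = 0.06/0.0468 = 1.28.
- Chance of a positive test about 25%, nearly all in favour of ISI, against 5% nominal.

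*Same, attribution 95% v 90%:*
- r1 = 0.38; r2 = 0.36; spurious difference 2 points.
- SE = sqrt[(0.2356 + 0.2304)/207] = 0.0474; z = 0.02/0.0474 = 0.42.
- Chance of a positive test about 7%.

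*Sensitivity:* with 5% dropout, 414 × 0.95 = 393, about 197 per arm. Assume p = 30% and 90% attribution in ERI, and count only false results in favour of ISI (critical value from the pooled variance).

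| Attribution in ISI | Recorded rates, ERI v ISI | Chance of a false ISI benefit |
|---|---|---|
| 90% | 27% v 27% | 2.5% |
| 80% | 27% v 24% | about 10% |
| 70% | 27% v 21% | about 29% |
| 60% | 27% v 18% | about 57% |

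At 70% attribution in ISI, varying p from 20% to 50% moves the chance from 19% to 53%. Equal attribution in the two arms gives no bias, a small gap does little, and a moderate gap matters.

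**The case against.** The strongest reply is that the article never says unrelated events go unrecorded. Saying that related events will be documented carefully does not exclude the others. The Follow-up section itself refers to Table 1 for its detailed schedule and items, and Table 1 drops the relatedness condition once radiotherapy starts. The analysis text is unrestricted, for serious events as well. The wording on late effects may simply describe what the RTOG/EORTC scheme scores. The article does not say who decides relatedness, and the full protocol or case report form may settle the matter.

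Much of this stands. A reader might infer that only related events are captured and that the contouring oncologist decides which ones count; the document establishes neither. A reader might also infer that toxicity evidence rests wholly on this step. It does not, because scheduled laboratory tests and patient questionnaires bypass it, and quality of life and immune function are also part of the expected benefit.

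What the reply does not remove is the conflict on the page. The only grading instructions are worded by cause, while the schedule and the analysis are not. Table 1 sets when reporting happens and does not say how an unrelated event is graded. Questionnaires do not replace clinician-graded CTCAE and RTOG/EORTC rates, and the article names condition-specific questionnaires for xerostomia and swallowing but none for neck fibrosis. These are statements in the article that conflict, not details it merely omits.

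**Conclusion.** The point holds as an inconsistency with a plausible direction of bias. The Follow-up and toxicity sections tie recording and grading to relatedness; Table 1 from the start of radiotherapy and the Statistical analysis section do not. With no clinician or assessor stated to be blinded, a relatedness judgement made before grading could favour ISI on clinician-graded toxicity, mainly for late effects and for acute events attributed to tumour or comorbidity.

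The stronger conclusion, that the plan will produce a false toxicity benefit, is not supported. Whether a filter operates is unsettled, and the size rests wholly on assumed attribution rates: about 7% false positives at 95% v 90% and about 25% at 95% v 80%, with an assumed 40% true rate and 207 per arm. It is worth correcting because the remedy is cheap and an ungraded event is hard to recover.

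**What to change.** Bring the Follow-up and toxicity sections into line with Table 1 and the Statistical analysis section:

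- Document and grade all adverse events, acute and late, at the visits already scheduled, regardless of cause.
- Record attribution (radiotherapy, chemotherapy, tumour, other) as a separate field after grading.
- State in the Statistical analysis section that the all-cause graded rate is the main between-arm comparison, with the treatment-related subset as supportive, and use the same order in reports to the Data Monitoring Committee.
- Table 1 needs no change from the start of radiotherapy.

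The cost is revised wording and somewhat more adverse-event entry, with no added visit, procedure or assessor. The change removes the relatedness filter but not the effect of unblinded grading. Recruitment began in August 2022 and was ongoing at publication, so if any sites have followed the narrower text, an early clarification limits what is lost.
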